### Baseline and follow-up measurements

Given the multiple etiologies in patients with FI, no test should be expected to yield consistent results in all patients with FI. Therefore, no standard protocol is available for the assessment and diagnosis of FI. The chosen tests at baseline (except for the questionnaires) are recommended by the American Gastroenterological Association, being procedures of value (symptom diary, physical examination, anal endosonography, anorectal manometry, rectal and anal sensory testing) and being procedures of possible value (defecography) [29]. As these diagnostic tests are part of the standard diagnostic assessment in the University Hospital Maastricht, participation in the trial will not burden the patient additionally. The following baseline measurements are done during the first and second patient visit:

▪ Vaizey incontinence score: this score reflects the severity of FI and ranges from 0 (complete continence) to 24 (complete incontinence) (Table 1) [28]. The Vaizey score is a widely used severity score and it is reported to be a reproducible score, which correlates highly with physicians' clinical impression [28]. Recently, it has also been demonstrated that higher Vaizey scores are associated with more reported problems in general health domains [30] and that changes in Vaizey score reflect patients' subjective perception of relief [31].

**Table 1 T1:** Fecal incontinence score according to Vaizey et al. [28]

Incontinent	Never	Rarely	Sometimes	Weekly	Daily
Solid stool	0	1	2	3	4
Liquid stool	0	1	2	3	4
Gas	0	1	2	3	4
Alteration in lifestyle	0	1	2	3	4
					
				No	Yes
Need to wear a pad or plug				0	2
Taking constipating medication				0	2
Lack of ability to infer defecation for 15 minutes				0	4

Minimum score = 0 = perfect continence; maximum score = 24 = totally incontinent Never: no episodes in the past 4 weeks; rarely: one episode in the past 4 weeks; sometimes: > 1 episode in the past 4 weeks, but < once a week; weekly: one or more episodes a week but < one a day; daily: one or more episodes a day

▪ Medical history: the medical history assesses gender, age, duration of complaints, risk factors (surgical, obstetric, neurological, metabolic) and medication use.

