### Co-interventions

After three months follow-up the physician evaluates the Vaizey score and the GPE-score. In case of an improvement of less than four points on the Vaizey score and/or a GPE-score of eight or nine, the clinician decides upon further therapeutic steps. If necessary, co-interventions are allowed after three months follow-up, although this should be avoided as much as possible. Examples of co-interventions are sacral nerve stimulation, anal repair or lavage. During physiotherapy treatment, patients are not allowed to use anal tampons.

The most common used drugs in patients with moderate to severe FI are Loperamid and sometimes Norit. Medical interventions and/or diet changes are first tried in the conservative management of patients with FI. If patients do not benefit from medical interventions, usual care implies referral for physiotherapy interventions. So, the majority of patients do not use drugs before physiotherapy management since they appeared not to be helpful. Nevertheless, patients who use drugs before starting with physiotherapy interventions are instructed to follow an unchanged stable medical regimen. Therefore, ongoing and change in medication use are monitored during the trial. In the analysis we will account for co-interventions, such as medication use.

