### Data analysis

In case of longitudinal missing data, imputation is performed with the last observation carried forward method. Main outcome is tested according to the intention to treat principle. Both treatment groups are checked for comparability regarding baseline data. An independent t-test is done for continuous variables and a Chi-square test for categorical variables. Analyses are performed to compare differences within groups between baseline and short-term follow-up (3 months) and long term follow-up (6 and 12 months) regarding primary and secondary outcome measures. A subgroup analysis is done for the patients with and without co-interventions. Analysis of variance is used to determine the difference in mean change of outcome measure between clinical subgroups. A two-tailed p-value of 0.05 is considered to indicate statistical significance. Data analysis is done using SPSS version 13.0 (SPSS, Inc., Chicago, Illinois). Confounders that are taken into account are presence of urinary incontinence, use of anal tampons, compliance and medication use.

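### The plan adjusts for, and splits patients by, co-intervention, compliance, tampon and medication use without restricting these to pre-randomisation values, which can bias the comparison of the arms

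*Protocol article*

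**What the plan says.** Three statements in the protocol article commit the analysis to conditioning on these variables.

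- Data analysis, on splitting: "A subgroup analysis is done for the patients with and without co-interventions".
- Data analysis, on adjustment: "Confounders that are taken into account are presence of urinary incontinence, use of anal tampons, compliance and medication use". The Bias and confounding section of the Discussion repeats the list.
- Co-interventions: "In the analysis we will account for co-interventions, such as medication use".

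Other sections show when the variables arise.

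- **Co-intervention.** The Co-interventions section says: "If necessary, co-interventions are allowed after three months follow-up, although this should be avoided as much as possible". The clinician considers further steps "In case of an improvement of less than four points on the Vaizey score and/or a GPE-score of eight or nine".
- **Compliance.** The Compliance section has it recorded at the start of every physiotherapy session. Bias and confounding says it determines the intensity of therapy and, through that, its success.
- **Medication.** Use before treatment is part of the medical history, but the Co-interventions section also says that "ongoing and change in medication use are monitored during the trial". Table 1 scores "Taking constipating medication" as 0 or 2 Vaizey points.
- **Tampons.** They are not allowed during physiotherapy, so any use after randomisation is a deviation or a later behaviour. Table 1 also gives 2 points for needing a pad or plug.

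Data analysis says separately that the main outcome is tested by intention to treat. It does not say that this test is free of the listed covariates, or that the conditioned analyses are exploratory.

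**The concern.** In a randomised comparison, a variable that arises after allocation cannot confound the effect of allocation. It may be a consequence of treatment, of the outcome, or of both. Once patients are split by it or adjusted for it, those compared across arms are no longer exchangeable.

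Each variable has its own difficulty. Compliance, by the article's own account, lies on the path from treatment to outcome. Co-intervention depends partly on the 3-month value of the primary outcome, so the two strata are enriched for responders and non-responders. Adjusting for on-trial constipating medication partly adjusts the Vaizey score for one of its own items.

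At stake are mainly the 6- and 12-month arm comparisons and, for compliance, every visit. The article intends the results to feed a physiotherapy guideline.

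**Working it through.** **1. The plan's own figure.** From the Sample size section: means 13.67 and 17 (difference 3.33), SDs 8.45 and 3.90, one-sided alpha 0.05, power 80%, drop-out 10%.

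n per arm = (8.45² + 3.90²)(1.645 + 0.842)² / 3.33² = 48.29. The total is 96.6, and 96.6 × 1.1 = 106.2 (stated: 106). With a difference of 4: 33.47 per arm, total 66.9, × 1.1 = 73.6 (stated: 73). These inputs are therefore the ones the plan uses. The sample size neither supports nor weakens the present point.

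**2. Inputs for the illustration.**

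- From the Sample size section: mean improvement 4.33 (arm 1) and 1 (arm 2).
- Common SD √((8.45² + 3.90²)/2) = 6.58, used as the SD of improvement (assumed).
- Assumed, not in the documents: normal distributions; the same mean improvement at 3 and 12 months; 3-to-12-month correlation ρ = 0.7; co-intervention given to a share s of patients improving by less than 4 points, chosen at random among them; no effect of co-intervention itself.

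**3. Formulas.** With c = (4 − μ)/σ, the expected 12-month improvement is

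- below 4 points at month 3: μ − ρσ φ(c)/Φ(c)
- at or above 4 points: μ + ρσ φ(c)/(1 − Φ(c))

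Here ρσ = 0.7 × 6.58 = 4.606.

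- Arm 1: c = −0.050, Φ = 0.480, φ = 0.3984. Below: 4.33 − 4.606 × 0.3984/0.480 = 0.51. Above: 4.33 + 4.606 × 0.3984/0.520 = 7.86.
- Arm 2: c = 0.456, Φ = 0.676, φ = 0.3596. Below: 1 − 4.606 × 0.3596/0.676 = −1.45. Above: 1 + 4.606 × 0.3596/0.324 = 6.11.

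If everyone below 4 points is treated (s = 1), the stratum with co-intervention gives 0.51 − (−1.45) = 1.96 and the stratum without gives 7.86 − 6.11 = 1.75. A linear model with arm and co-intervention averages the two with weights ab/(a + b), where a and b are the proportions of each arm in that stratum: 0.281 (with) and 0.200 (without). Adjusted difference: (0.281 × 1.96 + 0.200 × 1.75)/0.481 = 1.87.

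For s below 1, the untreated patients below 4 points join the stratum without co-intervention. At s = 0.5 its means are (0.520 × 7.86 + 0.240 × 0.51)/0.760 = 5.54 and (0.324 × 6.11 − 0.338 × 1.45)/0.662 = 2.25.

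**4. Results, true difference 3.33.**

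| Share of patients below 4 points treated | Without | With | Adjusted | Shortfall of adjusted value |
|---|---|---|---|---|
| All | 1.75 | 1.96 | 1.87 | 44% |
| Half | 3.29 | 1.96 | 2.91 | 13% |
| A quarter | 3.35 | 1.96 | 3.16 | 5% |
| A tenth | 3.35 | 1.96 | 3.27 | 2% |

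Simulation with 1,000,000 patients per scenario agrees within 0.02 for the all and half rows, and gives 3.32 to 3.34 for the comparison as randomised.

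**5. Sensitivity, all patients below 4 points treated.**

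- Correlation 0.5: adjusted 2.29. Correlation 0.9: adjusted 1.46.
- The plan's SDs, 8.45 and 3.90: +4.24 without, −0.50 with, 1.12 adjusted.
- Co-intervention worth 4 points: the difference as randomised is 3.33 − 4 × (0.676 − 0.480) = 2.55. The strata and adjusted values stay at 1.75, 1.96 and 1.87, matching neither 2.55 nor 3.33.
- No treatment effect and equal SDs: no bias.
- A 3-month comparison split the same way (SD 6.58) gives about 1.1 and 1.4 instead of 3.33.

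The documents give no inputs for the effect of adjusting for compliance, medication or tampon use, so that part rests on reasoning alone.

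**The case against.** The strongest reply is that the damage may be small. Co-intervention is a clinician's decision, is allowed only if needed, and is to be avoided where possible. A rule that treats everyone below 4 points is therefore an extreme. If a tenth of them are treated, the adjusted value falls short by only 2%, and the larger stratum is nearly unbiased. This stands. A reader might take about 45% as the expected loss, or treat the co-intervention split as the same thing as a split on the primary outcome. The text supports neither, because a poor 3-month result prompts the decision without fixing it.

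A reader might also infer that conditioning always shrinks a true effect. With the plan's unequal SDs one stratum is inflated and the other changes sign, so that inference fails too.

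Nor does the plan contradict its intention-to-treat statement. That statement governs who is analysed in which arm, and the co-intervention split is announced separately as a subgroup analysis. It does not, however, settle which covariates enter the comparison.

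Further, co-interventions are allowed only after month 3, so they leave the unsplit 3-month comparison untouched. Patients already on medication are told to keep it stable, most are said to use none, and baseline medication use is a legitimate covariate. All this is right, and narrows the point.

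Finally, the article names no model, and a fuller plan may exist. But the point does not rest on an omission. The article commits itself to accounting for these variables, and compliance with the exercises has no pre-randomisation value that could rescue it.

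**Conclusion.** The point holds in limited form. The article plans to adjust for or split by variables that arise, or can arise, after randomisation, and limits none of them to baseline. This can bias the arm comparison: mainly at 6 and 12 months for co-intervention (and at 3 months in any result split this way), and at all visits for compliance.

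Under the stated assumptions, a true 12-month difference of 3.33 becomes 1.9 to 3.3 after adjustment, depending on whether all or a tenth of the patients below 4 points receive a co-intervention. The stratum with co-intervention gives about 2.0 throughout. With the planned SDs and all such patients treated, the strata run from −0.5 to +4.2. Neither size nor direction can be known in advance. The bias vanishes when there is no treatment effect and the spread is equal.

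**What to change.** Reword the Data analysis and Co-interventions sections, and the matching text under Bias and confounding, so that:

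- the arms are compared as randomised at 3, 6 and 12 months, whatever co-intervention followed;
- adjustment uses only values measured before randomisation: baseline Vaizey score and, if wanted, baseline urinary incontinence and baseline medication use;
- compliance, on-trial medication, tampon use and co-intervention are removed as adjustment variables in the arm comparison;
- these four are reported by arm, and any split by co-intervention is labelled descriptive or exploratory and not presented as an estimate of treatment effect.

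The cost is wording only, and the planned 106 patients are unaffected. The small downside is that the 6- and 12-month effects become those of the treatment strategy including later care, which the report should say.

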### Secondary goals

Secondary goals of the PhysioFIT-study are to assess the psychometric properties of the PREFAB-score in clinical practice. In addition, baseline measurements are checked for their ability to predict outcome of physiotherapy.

Furthermore, the responsiveness of the Vaizey score is reviewed. The Vaizey score is a more common used severity score in surgical trials. But less is known about the responsiveness of the Vaizey score in physiotherapy trials. One study with comparable in- and exclusion criteria and study population made a first attempt to correlate the Vaizey score with a Global perceived effect score (31). Patients with a decrease of 9 points rated their situation "much better" than before physiotherapy treatment, patients with a decrease of 4 points rated their situation "better" and the group that rated their situation "(much) worse or equal" had a decrease in 1 point (patients were asked in a standardized interview to score their current situation on a scale of 1 (much worse), 2 (worse), 3 (no change), 4 (better), or 5 (much better)). We decided that rating the patients' situation as "better" is a minimally important change (MIC), expressed in an absolute number and not in a certain percentage.

Next to the Vaizey score we included the subjective GPE score (range 1–9) in our trial as an additional outcome measure, as we believe it is important to further investigate the responsiveness of the Vaizey score in patients with FI in physiotherapy trials.

Finally, it is expected that the outcome after physiotherapy interventions is dependent on the baseline Vaizey score; therefore we will perform a stratified analysis on baseline severity scores and change scores.

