### Spin off

Often, a trial is designed with the objective to make a difference in clinical daily practice. This section elaborates on what we believe might influence clinical practice.

Based on the results of this trial, baseline measurements are checked for their ability to be a prognostic factor for a good or poor outcome after physiotherapy. In this way, patients can be selected who benefit most of the proposed physiotherapy intervention. Furthermore, this trial can give information on the number of physiotherapy sessions after which more sessions are of no further benefit. Continuation or ending of therapy will have the same outcome at that point. Finally, if the effectiveness of a certain physiotherapy intervention is established, physicians can make a well-founded decision for referral to physiotherapy treatment, in stead of proceeding with surgical treatment. In conclusion, this trial might add to clearer referral patterns and better cooperation between physicians and physiotherapists.

In case of insufficient result of physiotherapy and proceeding to surgical treatment, the received physiotherapy intervention can still be of value. Patients already learned to be aware of their pelvic floor muscles and know how to contract them in an environment without post-surgical stress. Besides, their pelvic floor is probably in a better condition. Future research in this area can focus on the effect of different pre-operative physiotherapy interventions on the success of surgery in FI.

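### A check of prognosis is read as showing which patients benefit most, in a trial with no untreated arm and no stated arm-by-baseline interaction

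*Protocol article*

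**What the plan says.** Four places in the protocol article bear on the point.

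- **Data analysis.** "Analysis of variance is used to determine the difference in mean change of outcome measure between clinical subgroups". The clinical subgroups are not defined and no model terms are listed. The one split named there is by co-intervention: "A subgroup analysis is done for the patients with and without co-interventions". Change is otherwise described within groups: "Analyses are performed to compare differences within groups between baseline and short-term follow-up (3 months) and long term follow-up (6 and 12 months").
- **Secondary goals.** "In addition, baseline measurements are checked for their ability to predict outcome of physiotherapy". Because outcome is expected to depend on the baseline Vaizey score, "therefore we will perform a stratified analysis on baseline severity scores and change scores".
- **Spin off.** "baseline measurements are checked for their ability to be a prognostic factor for a good or poor outcome after physiotherapy". The next sentence draws the inference: "In this way, patients can be selected who benefit most of the proposed physiotherapy intervention".
- **Trial arms and patient selection**, with **Pelvic floor muscle training.** Every patient receives PFMT, one arm also receives RBT, and the comparison is said to give the additional effect of RBT.

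No section describes an interaction between arm and a baseline variable.

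**The concern.** A prognostic factor separates patients who end well from those who end badly. It does not say how they would have fared under another treatment. Some patients may improve more than others in both arms through natural course, measurement variation or milder disease, with no extra gain from the therapy. The Spin off section passes from the first idea to the second without a comparison that would support it.

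Baseline severity is the sharpest case. The baseline score is part of the change score, and patients enter only if that score reaches 12. Patients whose score was high partly by chance will tend to score lower later, whatever the treatment.

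The article intends the trial to inform a physiotherapy guideline and clearer referral. A rule about who benefits that reflects only prognosis or regression to the mean could direct patients towards or away from physiotherapy on no evidence of differential effect.

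**Working it through.** **1. What the design can identify.** Write the mean outcome for a patient with baseline profile x as m0(x) untreated, mP(x) on PFMT and mPR(x) on PFMT plus RBT.

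- Benefit of physiotherapy as a whole is m0(x) − mP(x) or m0(x) − mPR(x). With no untreated arm, m0(x) is never observed, so neither can be estimated for any x.
- Benefit of adding RBT is mP(x) − mPR(x). Randomisation identifies it. Whether it varies with x is the arm-by-x interaction.
- A prognostic check, or mean change by subgroup with arms pooled, estimates how average outcome varies with x. That can be large when mP(x) − mPR(x) is the same for every x.

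**2. The plan's own figure.** The article gives no number for any subgroup analysis. Its main calculation supplies the inputs used below.

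- SDs 8.45 and 3.90, difference 17 − 13.67 = 3.33, one-sided alpha 0.05, power 80%, dropout 10% (Sample size).
- Average SD = √((8.45² + 3.90²)/2) = √43.31 = 6.58.
- n per arm = 2 × 43.31 × (1.645 + 0.842)² / 3.33² ≈ 48.3. Rounded down to 48, this is 96 in total, and 96/0.9 = 106.7, which matches the stated 106. Rounding up to 49 gives 98/0.9, that is 109, within 3%.

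So 96 is the evaluable number behind the stated 106.

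**3. Regression to the mean in the severity strata, arms pooled.** From the article: entry at Vaizey 12 or more, and a scale maximum of 24. Assumed: pre-selection mean 16 and SD 4.5, baseline/follow-up correlation r from 0.4 to 0.8, 1:1 allocation, and an identical arm effect in every patient. The test compares mean change in the upper and lower halves of baseline at two-sided 0.05, with n = 96.

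| r | Spurious extra improvement, more severe half | Comparison significant |
|---|---|---|
| 0.4 | about 3.0 points | about 88% |
| 0.5 | about 2.5 points | about 79% |
| 0.6 | about 2.0 points | about 66% |
| 0.8 | about 1.0 point | about 32% |

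The middle column follows (1 − r) × the baseline gap between halves. The gap is about 5.0 points, since 3.0/0.6 = 1.0/0.2 = 5.0; at r = 0.5 this gives 0.5 × 5.0 = 2.5. With n = 106 the significance rates are 91%, 72% and 35% at r = 0.4, 0.6 and 0.8. The true difference in benefit is zero throughout. The arm-by-half interaction test rejects in about 5% of the same trials, with an average estimate near zero, because the artefact is common to both arms and cancels.

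For scale, the article takes 4 points as the minimally important change on the Vaizey score.

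**4. What the interaction test could detect.** Assume two equal subgroups, SD 6.58 and two-sided 0.05.

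- SE of the interaction = 2 × 6.58 × √(4/106) = 2.56 points.
- Power for 3.33 points = Φ(3.33/2.56 − 1.96) ≈ 26%; for 4 points, about 35%. With 95 evaluable: 23% and 32%.
- Detectable at 80% power: (1.96 + 0.842) × 2.56 ≈ 7.2 points.
- Evaluable patients needed for 80% power: about 491 for 3.33 points, 340 for 4 points.

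These figures make no allowance for the gain from adjusting for baseline.

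**The case against.** The article already uses prognostic language for most of this work, in the Secondary goals section and in the first part of the Spin off passage. Pooling arms is a legitimate way to study prognosis. The selection sentence stands in a discussion of possible influence on practice, not among the hypotheses, and the guideline statement does not mention subgroups. All of this stands, and it limits the point to one inference and the analyses that would feed it.

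Four stronger readings are tempting, and the document does not support them.

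- A reader might infer that the article claims these analyses show who gains from RBT. The sentence refers to the proposed physiotherapy and does not name RBT. If physiotherapy as a whole is meant, there is no comparator for it; if the combined arm is meant, an interaction is needed. The inference fails either way.
- A reader might infer that the subgroup ANOVA leaves out the treatment arm. The text is silent. An ANOVA can contain arm and an interaction, the severity analysis could be an arm comparison within strata, and a fuller plan may say so. The ANOVA sentence itself makes no claim about benefit.
- A reader might infer that regression to the mean distorts every subgroup comparison. It acts chiefly on the baseline Vaizey strata, and on other subgroups only as far as they differ in baseline score.
- A reader might count any significant pooled subgroup difference as a false positive. A real 3-point prognostic difference with 48 per subgroup would be detected about 59% of the time. That is power to find a true prognostic factor, and the error arises only when the result is called benefit.

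An unseen analysis plan could add the interaction. It would not repair the Spin off sentence, which derives selection by benefit from prognosis alone. The fault is therefore a stated inference, not an omitted detail.

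**Conclusion.** The point holds in this form: the Spin off section draws a conclusion about who benefits from a check that can show only prognosis. No section states the arm-by-baseline interaction that could support such a conclusion for added RBT, and for physiotherapy as a whole the design cannot support one. This needs no numerical assumption, only that both arms receive PFMT and there is no untreated arm.

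The size in the severity strata is conditional. If arms are pooled, about 3.0 to 1.0 spurious points and significance in about 88% to 32% of trials follow from the assumed correlations of 0.4 to 0.8, mean 16 and SD 4.5, none of which the article gives. Ignoring the entry threshold would overstate it: at a correlation of 0.5 the rate would be 99%, against about 79% with the threshold applied. The randomised comparison of the two arms on the Vaizey score is not affected. The point should be corrected before the secondary results are interpreted, but it does not threaten the trial's main question.

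**What to change.** 1. Describe the baseline-predictor analyses and the comparisons of change between subgroups as prognostic only.
2. Remove the Spin off sentence on selecting patients, or reword it to say that baseline measurements may indicate expected outcome after physiotherapy.
3. For any statement about who gains from added RBT, including the analysis by baseline severity, model follow-up Vaizey score on baseline Vaizey score, arm, subgroup and arm-by-subgroup. Report the interaction with its confidence interval and label it exploratory.

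The cost is one extra model term per subgroup and some rewording, with no new data or patients. The drawback is low power: about 26% at 106 patients for an interaction of 3.33 points, which is as large as the whole effect used to size the trial. A non-significant interaction should therefore not be reported as evidence that RBT works equally in all patients.
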